#### Evaluation and Assessment Frameworks

We will use the following assessment instruments:

Mini-Mental State Examination: It verifies the integrity of cognitive functions, assessing the functions of space-time orientation, memory, attention, calculus, language, and constructive praxis. It includes 11 tasks, with a score ranging from 0 to 30 points. Brucki et al [23] adapted it to the Brazilian context. The cut-off points relate to the years of schooling of the subjects, ie, for illiterate individuals, 19 points; 1-3 years of schooling, 23 points; 4-7 years of schooling, 24 points; and more than 7 years of schooling, 28 points.Sample characterization and sociodemographic questionnaire: It includes questions on age, level of education, income, and experience in using a blood pressure meter. The project researchers will provide the specifications.Martín-Bayarre-Grau questionnaire (MBG): It assesses the therapeutic adherence for arterial hypertension. Alfonso et al [24] developed and validated this instrument, and Matta et al [25] adapted it to the Brazilian Portuguese language.Dietary intake questionnaire by the Brazilian Food and Nutrition Surveillance System (SISVAN): from the Brazilian Ministry of Health [26], this questionnaire identifies the intake frequency of some foods and beverages over the last 7 days through 10 questions. Each item may relate to healthy food or nonrecommended unhealthy food.Engagement questionnaire: It assesses the attributes of engagement, such as esthetics, sensory appeal, concentration, awareness, challenge, control, feedback, interest, motivation, novelty, and time perception. O’Brien and Toms [27] proposed and validated the model, and Cechetti et al [17] translated it to Portuguese.Acceptance questionnaire: This is based on the technology acceptance model (TAM) [28]. The assessment relies on three categories: perceived utility (determines the degree to which a person believes the use of a technology may improve performance and productivity), ease of use (determines the degree to which a person believes the use of a system will be easy to learn and interact with), and external variables (provide understanding about what influences perceived utility and ease of use).Usability assessment questionnaire: This is in accordance with the System Usability Scale (SUS), related to the ease of use and use effort. Brooke [29] developed this framework.Comfort assessment questionnaire for the wearable device: It aims to verify the comfort and well-being of users while trying the wearable technology. The project researchers will produce this instrument.Characteristics of app use: It considers the number of accesses, number of records per period, response to notifications, and reminders. The system usage logs will calculate all this information. We will also use open questions so that participants can report their experience.Health professional assessment: We will perform a semistructured interview with health professionals to verify opinions on the characteristics and resources of the eHealth platform. Questions include, but are not limited to the following: (1) As a health professional, do you believe that the app and dashboard’s features can facilitate the clinical practice to monitor a patient? In what way? (2) Do you believe that a patient can benefit from the app’s features in his or her treatment? In what way? (3) What changes do you suggest for this platform to make it more useful or applicable to clinical practice?

#### Procedure

We will collect data at three timepoints: preintervention, during the intervention, and postintervention. We will develop the wearable device and assess it in parallel outside the clinical trial.

#### Preintervention Period

After verifying the inclusion criteria, all participants will have a 1-hour meeting with the researchers for instructions on the objective of the study and for signing a consent form detailing all the study procedures. We will register the participants of the intervention group in the system and instruct them about the app’s use. We will collect the preintervention data from both groups from a sample characterization questionnaire and an MBG questionnaire [24].

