#### Mobile App

The app allows users to record their data, send and receive notifications, communicate with their medical team, and pair the wearable device that will be developed. After installation and first registration, the patient can access the main interface containing his or her last measurements. Through the main interface, users can access the menu with the list of functionalities available, which include height, physical activity, heartbeat, waist, body fat, mood, weight, blood pressure, sleep, reminders, and chat. In the new version, other records will be available, including dietary intake and improvement of physical activity data. When selecting a functionality, patients can view their record information and graphs, and they may include, change, or delete data.

For the measurements, the patient records the date, time, value, and an optional observation. All operations with patient data synchronize with the central server. Periodically, the app displays alert notifications and reminders on the health data recorded, including notes sent by the health professional. Each notification presents a title, a brief description, and buttons with *yes* and *no* options. When clicking *yes*, the system sends the information to the server, showing whether the patient completed the action or reminder presented, for instance, whether they took the medication or visualized the message from the health professional. Such integration aims at continuous monitoring and the stimulus to maintain healthy practices.

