#### Study Population and Sample

The study population will include men and women under treatment for arterial hypertension who will be assisted by health professionals in the public health system of a Brazilian city. After the invitation to take part in the study, the participants will sign a consent form. The effect (primary outcome) is expected to be 80% in the intervention group and 40% in the control group, which means a 40% difference. These proportions are based on the findings of the study by Neumann et al [22], which was conducted with a similar design, and also on more optimistic results obtained from one of our pilots [19]. For sample calculation, we used Epi Info version 6.0 software (Centers for Disease Control and Prevention, Atlanta, Georgia; sample size/2 proportions). We considered an estimate of 40% proportion difference between groups, 95% confidence interval, and 80% statistical power (beta). The calculation resulted in 28 individuals for each group, but to minimize the effects of loss and refusal during the intervention, we added 20% to the size, yielding a total of 34 individuals in each group.

The allocation of patients in each group will be based on the eligibility criteria. For example, if the patient fits all the criteria but does not have a mobile phone compatible with the app, then he or she will be allocated to the control group. If the patient has a mobile phone compatible with the app, he or she will be allocated to the intervention group. For propensity score calculation, based on the effect of confounding factors or predictors of exposure (to intervention), we will consider demographic variables of age, gender, and socioeconomic status.

We will consider the following inclusion criteria:

Cognitive ability confirmed by the Mini-Mental State Examination [23] (both groups)Current medical monitoring for the treatment of hypertension in the public health system of the city of Passo Fundo, RS, Brazil (both groups)Possibility to measure blood pressure in drugstores, hospitals, Family Health Strategies, or centers for comprehensive health care (both groups)Possession of an Android mobile phone, version 4.3 or higher (intervention group)Familiarity with the use of apps (intervention group)Internet access on the smartphone (intervention group).

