#### Intervention Period

Participants from the control group will perform conventional hypertension monitoring using paper logbooks. Participants from the intervention group will use the app for 3 months, periodically registering the values of blood pressure, weight, height, sleep quality, waist circumference, mood, and heartbeats, among others. Health professionals from the health centers will assist the participants by using the website dashboard to monitor and interact with their patients. Professionals’ performance will not be evaluated, but we will ask them to participate by communicating with patients weekly on the platform. We will use all the data recorded by patients and health professionals during the intervention in the final analysis of results, especially the measurements of blood pressure and frequency of physical activity.

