#### Postintervention Period

All participants will have a 1-hour meeting with the researchers for the final data collection. We will collect the postintervention data with an MBG questionnaire [24], an engagement questionnaire [27], an acceptance questionnaire (TAM) [28], and a usability questionnaire (SUS) [29].

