#### Statistical and Qualitative Analysis

Our expectation for the primary outcome is the reduction and stabilization of blood pressure. For the secondary outcome, we hope for acceptance of the eHealth platform and improvements in treatment adherence, physical activities, and dietary intake. A priori levels will be set according to the assessment tool and the expected outcome. The acceptance of the eHealth platform will consider good scores obtained in the analysis of usage logs and questionnaires of engagement, SUS, and TAM. Improved adherence to treatment will consider MBG questionnaire scores measured before and after the intervention. For the analysis of physical activities and dietary intake, a binary outcome will consider whether the patient has adequate levels, diagnosed according to the SISVAN’s questionnaire and standards.

For qualitative data, we will use Minayo’s guidelines [30]. Numeric data will be analyzed with statistical software SPSS 22 (IBM Corp, Armonk, New York). We will calculate the measures of central tendency and dispersion of the quantitative variables, and we will use the Kolmogorov-Smirnov test to verify normality. Basic quantitative data will be determined by mean, standard deviation, and median. Categorical data will be determined by simple frequency. Blood pressure data will be analyzed with the paired *t* test. Either the paired *t* test (parametric) or the Wilcoxon test (nonparametric) may be applied to compare other quantitative variables before and after the intervention. To assess treatment adherence, physical activity, and dietary intake after intervention, we will apply the Chi-square test while considering the app use as the dependent variable; the independent variables will be treatment adherence, physical activity, and dietary intake. For the MBG questionnaire, we will apply the Mann-Whitney test to compare the score between the groups before and after the intervention. The same test may be used to compare diastolic and systolic blood pressure measurements between the preintervention and postintervention groups. We will consider a 95% confidence interval (*P*<.05).

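### Blood pressure is the primary outcome, but the text names no common pre or post reading; the only stated source is recorded through different channels in the two groups

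*Protocol article*

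**What the plan says.** The Statistical and Qualitative Analysis section of the protocol article states: "Our expectation for the primary outcome is the reduction and stabilization of blood pressure". It plans a paired t test for blood pressure and allows a Mann-Whitney test of systolic and diastolic values before and after. The Abstract (Methods) promises a comparison in both groups at three stages: before, during and after.

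The data listed for each stage are:

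- **Preintervention Period:** "We will collect the preintervention data from both groups from a sample characterization questionnaire and an MBG questionnaire". Evaluation and Assessment Frameworks says of the characterization questionnaire: "It includes questions on age, level of education, income, and experience in using a blood pressure meter". No pressure value is mentioned.
- **Intervention Period, app group:** "Participants from the intervention group will use the app for 3 months, periodically registering the values of blood pressure", along with other measures.
- **Intervention Period, control group:** "Participants from the control group will perform conventional hypertension monitoring using paper logbooks". The section adds that everything patients and health professionals record in this period enters the final analysis, and it singles out blood pressure.
- **Postintervention Period:** "We will collect the postintervention data with an MBG questionnaire", followed by the engagement, technology acceptance and usability questionnaires.

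The Mobile App section describes reminders and notifications, and alerts when an entry departs from guideline patterns. It says of patients and their records that "they may include, change, or delete data". The Website Dashboard section gives the clinician a real-time view of the entries.

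Study Population and Sample has this inclusion criterion, marked as applying to both groups: "Possibility to measure blood pressure in drugstores, hospitals, Family Health Strategies, or centers for comprehensive health care".

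**The concern.** A before/after test needs a before value and an after value obtained in the same way in both groups. The text itemises what each visit collects, and blood pressure is on neither list. Followed as written, the primary outcome would come from records kept during the intervention.

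In one group those records are made inside the product under test. That product reminds the patient, flags abnormal entries, shows them to a clinician who is asked to communicate weekly, and lets the patient alter them. Nothing comparable is described for the paper logbook. How often readings are recorded, and which of them survive, could therefore differ between groups with no true difference in pressure. The trial is neither randomized nor blinded, so nothing else in the design would separate such a difference from an effect.

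There is also a problem of timing. If the first available reading falls after the app has been issued, it is not a clean baseline, and a missed baseline cannot be recovered later.

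**Working it through.** **1. Where blood pressure appears in the text**

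| Stage | Comparison promised (Abstract; Statistical and Qualitative Analysis) | Data listed | Blood pressure listed? |
|---|---|---|---|
| Before | Yes, both groups | Characterization questionnaire, MBG | No |
| During | Yes, both groups | App entries or paper logbook; records by professionals | Yes, through different channels |
| After | Yes, both groups | MBG, engagement, TAM, SUS | No |

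The instrument list in Evaluation and Assessment Frameworks has no blood pressure measurement either. The promised before and after values thus have no stated source.

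**2. What differs between the groups**

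- Permitted places of measurement: the same.
- Device, number of readings and timing: not stated for either group.
- Recording channel: app versus paper.
- Reminders and alerts tied to the entries: described for the app only.
- Clinician's view of entries in real time: described for the app only.
- Editing by the patient: stated for the app; nothing is said about paper.

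The documented difference is in recording, prompting and visibility. A difference in the physical measurement is not shown.

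**3. The plan's own sample size**

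Inputs from Study Population and Sample: 80% versus 40%, 95% confidence (read as two-sided 0.05), 80% power.

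- Uncorrected: n = [1.96·√(2·0.6·0.4) + 0.8416·√(0.8·0.2 + 0.4·0.6)]² / 0.4² = 22.33.
- With continuity correction: (22.33/4)·[1 + √(1 + 4/(22.33·0.4))]² = 27.1, rounded up to 28.
- With 20% added: 28 × 1.2 = 33.6, rounded up to 34 per group, 68 in total.

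The stated 28 and 34 reproduce. I use 28 per group below.

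**4. Hypothetical size on the mmHg scale**

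Assumptions not in the document: SD 15 mmHg, and a bias b that comes only from recording. The test is a two-sided comparison of group means with no true effect.

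SE = 15·√(2/28) = 4.01 mmHg. False positive rate = Φ(−1.96 + b/SE) + Φ(−1.96 − b/SE).

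| b (mmHg) | b/SD | b/SE | False positive rate |
|---|---|---|---|
| 0 | 0 | 0 | 5% |
| 2 | 0.13 | 0.50 | 0.072 + 0.007 = 8% |
| 4 | 0.27 | 1.00 | 0.168 + 0.002 = 17% |
| 5 | 0.33 | 1.25 | 0.238 + 0.001 = 24% |

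The rate depends on b only through b/SD. The b/SD column therefore holds for any SD; a larger SD makes a given bias in mmHg matter less, and a smaller SD makes it matter more.

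**5. Hypothetical size on the success/failure scale used for sizing**

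Assume true success is 40% in both groups, and that a share q of true failures in the app group is recorded as success. Then p = 0.4 + 0.6q and the spurious difference is d = 0.6q. With the mean proportion m = (p + 0.4)/2, SE₀ = √(m(1−m)·2/28) and SE₁ = √([p(1−p) + 0.24]/28). The false positive rate is Φ((d − 1.96·SE₀)/SE₁) + Φ((−d − 1.96·SE₀)/SE₁).

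For q = 20%: p = 0.52, d = 0.12, SE₀ = 0.1332, SE₁ = 0.1322, rate = Φ(−1.07) + Φ(−2.88) = 14.5%.

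| q | Spurious difference | False positive rate |
|---|---|---|
| 0 | 0 points | 5.0% |
| 5% | 3 points | 5.6% |
| 10% | 6 points | 7.3% |
| 20% | 12 points | 14.5% |
| 30% | 18 points | 26.7% |

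Both tables show only how sensitive a trial of this size would be. Neither estimates a bias in this trial.

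**The case against.** The strongest reply is that this is a condensed article and the visit lists are loose summaries. The SISVAN dietary questionnaire decides a secondary outcome, yet it is missing from both lists, so the lists may be incomplete. The trial flowchart (Figure 2) is not shown and could include a blood pressure reading. The Abstract does promise pressure at all three stages. All of this stands, and it is why one cannot say that no baseline will be taken. It does not remove the problem: the text names a source for the blood pressure data, and that source is the records made during the intervention.

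Other parts of the reply also stand:

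- A reader might infer that pressure is physically measured differently in the two groups. The document does not support this, because the permitted places are the same and no device is named.
- A reader might infer that the outcome is wholly self-reported. The text also counts data recorded by health professionals, though it does not describe standard readings by them at fixed times in both groups.
- Editability is not proof of bias. Paper entries can be altered or left out too, and the document says nothing either way.
- The magnitudes rest on an assumed SD, assumed biases or assumed misclassification. They concern a between-group test, whereas the main test named for blood pressure is paired, with Mann-Whitney as an option.

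**Conclusion.** The point holds as a conflict within the text that bears on the primary outcome. The promised before/after comparison has no stated common baseline or endpoint reading, and the only stated source of blood pressure passes through a recording channel that in one group is part of the intervention. This goes beyond missing detail, because the text itemises each visit and says which records feed the final analysis.

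The document does not establish that a bias exists, how large it would be, or which group it would favour. The illustrative range, a false positive rate of about 8% to 24% instead of 5%, rests on an assumed SD of 15 mmHg, 28 per group, a recording bias of 2 to 5 mmHg and a between-group comparison of means. The finding would shrink to a request for consistent wording if Figure 2 or the full protocol already specifies identical readings at both meetings.

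**What to change.** Reconcile the Preintervention and Postintervention Period sections with the Abstract and the analysis section, and with Figure 2:

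1. State that blood pressure is measured in both groups at the two 1-hour meetings with the researchers, with the same device and the same written procedure, and that the first measurement is taken before the app is put to use.
2. Name those two values as the primary baseline and endpoint.
3. Keep app and logbook readings as supportive data for the comparison during the intervention, and report how many readings each participant contributed by group.
4. Correct the visit lists at the same time, including where the SISVAN questionnaire is completed.

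Both groups already attend both meetings, so the cost is a few minutes per visit, a common device and a small amendment. It needs to be in place before the first participant is enrolled.

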#### Intervention Period

Participants from the control group will perform conventional hypertension monitoring using paper logbooks. Participants from the intervention group will use the app for 3 months, periodically registering the values of blood pressure, weight, height, sleep quality, waist circumference, mood, and heartbeats, among others. Health professionals from the health centers will assist the participants by using the website dashboard to monitor and interact with their patients. Professionals’ performance will not be evaluated, but we will ask them to participate by communicating with patients weekly on the platform. We will use all the data recorded by patients and health professionals during the intervention in the final analysis of results, especially the measurements of blood pressure and frequency of physical activity.

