**Methods:**

The platform will include a server that centralizes all the data and business rules, a website dashboard for health professionals, and a mobile app for patients. We will analyze the effects of its use through a controlled, nonrandomized, nonblind, prospective, monocentric clinical trial. We will enroll 68 participants diagnosed with arterial hypertension and under medical follow-up and categorize them into two groups. The participants of the intervention group will use the platform as a monitoring method, whereas the participants of the control group will use conventional methods. In both groups, we will assess and compare the evolution of blood pressure and treatment adherence before, during, and after the intervention.

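### The promised before/during/after blood pressure comparison uses all recorded readings, but the named tests take one pair or one value per patient, and nothing says how the readings become a patient-level value

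*Protocol article*

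**What the plan says.** Three places in the protocol article describe longitudinal blood pressure data.

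- Abstract, Methods: in both groups, "we will assess and compare the evolution of blood pressure and treatment adherence before, during, and after the intervention".
- Procedure: "We will collect data at three timepoints: preintervention, during the intervention, and postintervention".
- Intervention Period: "Participants from the intervention group will use the app for 3 months, periodically registering the values of blood pressure" among other measures, while controls keep paper logbooks. The section adds that "We will use all the data recorded by patients and health professionals during the intervention in the final analysis of results", and names blood pressure as one of the two measures of most interest.

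The section Statistical and Qualitative Analysis then fixes the method: "Blood pressure data will be analyzed with the paired" t test. After assigning the Mann-Whitney test to the adherence score, it adds: "The same test may be used to compare diastolic and systolic blood pressure measurements between the preintervention and postintervention groups". The significance level is P<.05.

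The rest of that section offers a chi-square and I² check of heterogeneity and, if feasible, a logistic regression with app use as the dependent variable. It also allows techniques to be changed to suit the collected data. It names no repeated-measures method and no per-patient summary.

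**The concern.** Blood pressure is the primary outcome, and the stated test does not fit the stated comparison. A paired t test works on one difference per patient within a group. It has no place for a third period, and on its own it does not compare the groups. A Mann-Whitney test does compare groups, but it assumes one independent value per patient.

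Whoever runs the analysis must therefore decide how 3 months of readings become something these tests accept, and the article leaves that open. Two of the possible choices are poor. If only one value before and one after are used, the readings made during the intervention contribute nothing and the promised comparison is not made. If every reading is entered as a separate observation, readings from the same patient count as different patients and the standard errors are too small. Patients who record often would also dominate, and the app's reminders may make recording more frequent in one group than in the other.

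**Working it through.** **The plan's own figure.** The only computed figure is the sample size. "The effect (primary outcome) is expected to be 80% in the intervention group and 40% in the control group"; with two-sided 5% and 80% power, the two-proportion formula gives 23 per group without continuity correction and 28 with it, which matches the article. Adding 20% gives 28 × 1.2 = 33.6, so 34. The present point does not affect this number.

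**Inputs for the illustration.**
- From the article: 28 per group before loss, and P<.05 (sidedness not stated; taken as two-sided).
- Assumed, because the article does not give them: m readings per patient (3, or 12 for roughly weekly over 3 months), a common within-patient correlation rho of 0.3 to 0.7, and no true effect.

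**Pooling readings between groups.** Treating m readings per patient as independent understates the variance of a group mean by the design effect DE = 1 + (m − 1) × rho. The false-positive rate is then 2 × [1 − Φ(1.96 / √DE)].

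| m | rho | DE | 1.96/√DE | Rate by formula |
|---|---|---|---|---|
| 3 | 0.3 | 1.6 | 1.55 | 12.1% |
| 3 | 0.5 | 2.0 | 1.39 | 16.6% |
| 3 | 0.7 | 2.4 | 1.26 | 20.6% |
| 12 | 0.3 | 4.3 | 0.95 | 34.5% |
| 12 | 0.5 | 6.5 | 0.77 | 44.2% |
| 12 | 0.7 | 8.7 | 0.66 | 50.6% |

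Simulation agrees. With 28 per group, a t test on pooled readings (10,000 runs per setting) gave 12.4%, 17.0% and 21.0% for m = 3, and 33.9%, 44.8% and 51.4% for m = 12. Mann-Whitney was similar. With 34 per group the highest value for m = 3 was 22.1%.

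Outside the assumed range the rate moves a long way. At rho = 0.1 it is 7.4% (m = 3) and 17.6% (m = 12). With 90 daily readings and rho = 0.5 it is 77%.

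**Pooling readings in the paired t test.** The result depends on how pairs are formed. If each of m readings is set against one shared baseline, the differences within a patient correlate at 0.5 whatever rho is. DE is then 2.0 for m = 3 and 6.5 for m = 12, giving 16.6% and 44.2% (simulated at rho = 0.5: 16.1% and 45.0%). If each reading has its own separate baseline reading and patients do not differ in their true change, there is no inflation: simulation gave about 5%.

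**One mean per patient.** In the same 28-per-group simulations, a t or Mann-Whitney test on patient means gave 4.4–5.4% in every setting, with every reading used.

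**Precision from extra readings.** Relative to a baseline-adjusted comparison of one follow-up reading, the mean of k readings has variance [(1 + (k − 1) × rho)/k − rho²] / (1 − rho²). At k = 3 and rho = 0.5 this is (0.667 − 0.25)/0.75 = 0.56, and it runs from 0.49 to 0.61 over rho 0.3 to 0.7. For an end-of-3-months contrast in a model with group-by-period terms and complete data, the ratio was 1.00 in simulation (300 runs): the earlier readings add essentially nothing to that contrast.

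**Baseline in a mixed model.** If the before reading is both an outcome row and a covariate, the test of the after contrast is no longer valid. With 28 per group, rho = 0.5, two during readings and one after reading, 920 runs gave 7.6% false positives, against 5.0% with the before rows removed.

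**The case against.** The strongest reply has three parts.

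1. **No place in the article says that readings will be pooled.** The analysis section speaks of values before and after the intervention. A sensible analyst could average each patient's readings per period, use all the data, keep the named tests and hold about 5%. This stands. A reader might infer that the plan must either count readings as independent or discard them, or that it carries a false-positive rate of 16–45%. The article supports neither. Averaging is a third route that it does not exclude, and those percentages correspond to an assumed correlation of 0.5 with 3 to about 12 readings.

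2. **Using all recorded data may cover more than hypothesis tests**, including usage logs and descriptive summaries, and the choice of reading is detail for a fuller plan. This stands in part. An article need not define every derived variable. But this one does name the blood pressure test, and that test does not deliver the three-period comparison promised in the Abstract. The clause allowing techniques to be adjusted does not close the gap, because it leaves the primary analysis to be chosen once the data are in hand.

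3. **The paired t test does respect the patient**, since differencing removes the patient's own level. That is right for one pair per patient. The difficulty begins when several readings per patient must enter.

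**Conclusion.** The point holds as a mismatch between the promised comparison and the named tests. The article commits to comparing blood pressure before, during and after the intervention from all readings, and names tests that cannot do so unless the readings are first summarised per patient. No such step is stated.

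The error rates of about 12–22% (3 readings) and 35–51% (12 readings) show what pooling would cost with 28 per group, equal correlation between readings and rho of 0.3 to 0.7. They describe one possible analysis and are not a property of the plan.

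A reader might also infer that using all readings would lift power from 80% to about 96%. That follows from the 0.56 variance ratio only for a contrast averaged over three follow-up readings. It does not apply to an end-of-3-months contrast, and the article's 80% refers to a comparison of two proportions, not to a mean difference.

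**What to change.** In Statistical and Qualitative Analysis, make the patient the unit of analysis for blood pressure.

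- **Preferred:** reduce each patient's readings to one mean per period (before, during, after). Compare the groups on the follow-up mean, adjusted for the before value by analysis of covariance, and name this as the single primary contrast.
- **Alternative:** a linear mixed model of the follow-up readings (during and after) with a patient random intercept, group, period, group-by-period and the before value as a covariate. The before reading must not also enter as an outcome. Name one contrast as primary.

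In either case, claim a gain in precision from the extra readings only if the named contrast is averaged over follow-up.

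The cost is a few sentences and a little programming in SPSS 22, the package already named. No new patients or data are needed. The small downside of the mixed model is that it relies on a working correlation structure and on skipped readings being missing at random.
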